## Abstract

**Background:**

The hormone cortisol plays important roles in human circadian and stress physiology and is an interesting target for interventions. Cortisol varies not only in response to stress but also as part of a diurnal rhythm. It shows a particularly sharp increase immediately after awakening, the cortisol awakening response (CAR). Cortisol can be affected by medication, but it is less clear whether it can also be affected by learning. Animal studies have consistently shown that cortisol can be affected by pharmacological conditioning, but the results in humans have been mixed. Other studies have suggested that conditioning is also possible during sleep and that the diurnal rhythm can be conditioned, but these findings have not yet been applied to cortisol conditioning.

**Objective:**

The objective of our study was to introduce a novel avenue for conditioning cortisol: by using the CAR as an unconditioned response and using scent conditioning while the participant is asleep. This study investigates an innovative way to study the effects of conditioning on cortisol and the diurnal rhythm, using a variety of devices and measures to make measurement possible at a distance and at unusual moments.

**Methods:**

The study protocol takes 2 weeks and is performed from the participant’s home. Measures in week 1 are taken to reflect the CAR and waking under baseline conditions. For the first 3 nights of week 2, participants are exposed to a scent from 30 minutes before awakening until their normal time of awakening to allow the scent to become associated with the CAR. On the final night, participants are forced to wake 4 hours earlier, when cortisol levels are normally low, and either the same (conditioned group) or a different (control group) scent is presented half an hour before this new time. This allows us to test whether cortisol levels are higher after the same scent is presented. The primary outcome is the CAR, assessed by saliva cortisol levels, 0, 15, 30, and 45 minutes after awakening. The secondary outcomes are heart rate variability, actigraphy measures taken during sleep, and self-reported mood after awakening. To perform manipulations and measurements, this study uses wearable devices, 2 smartphone apps, web-based questionnaires, and a programmed scent device.

**Results:**

We completed data collection as of December 24, 2021.

**Conclusions:**

This study can provide new insights into learning effects on cortisol and the diurnal rhythm. If the procedure does affect the CAR and associated measures, it also has potential clinical implications in the treatment of sleep and stress disorders.

**Trial Registration:**

Netherlands Trial Register NL58792.058.16; https://trialsearch.who.int/Trial2.aspx?TrialID=NL7791

**International Registered Report Identifier (IRRID):**

DERR1-10.2196/38087

## Introduction

### Background

The hormone cortisol has far-reaching effects throughout the body, mainly influencing metabolism but also being involved in systems as varied as the immune system [1], memory [2,3], and the sleep-wake cycle [4]. Cortisol is secreted from the adrenal gland as the end product of the hypothalamic-pituitary-adrenal (HPA) axis, a system of cascading secretions that originate in the hypothalamus. Cortisol is perhaps best known for its role in the stress response [5], and thus is often called the “stress hormone” in everyday parlance. However, cortisol does not just fluctuate in response to stress; it also follows several rhythms, including a diurnal rhythm. Cortisol levels are highest in the early morning and decline throughout the day and evening, with levels increasing again in the second half of the night [6]. A visual representation of a typical rhythm is shown in Figure 1. The onset of pulsatile secretion varies, but a strong peak is seen in cortisol increase in the period immediately after awakening in most participants [7]. This peak is referred to as the cortisol awakening response (CAR). The CAR has been extensively studied and has been shown to be generally consistent in size within an individual [7,8] but also influenced by situational variables [9], such as sleep duration in the preceding night [10]. Befitting the role of the stress hormone, the most reliable of the situational variables are stress-related [11]. Reviews of relevant studies suggest that the CAR is partially responsible for preparing the body in anticipation of the events and challenges of the day ahead [9,10]. Anticipation of a stressful and challenging day may lead to an increased CAR [12], while an intervention that reduces stress showed a corresponding decrease in the CAR [13]. Meanwhile, patients with severe amnesia, presumably not expecting anything from the coming day, seem to show no CAR at all [14].

Apart from stress and diurnal rhythms, cortisol levels can also be influenced more directly by medical interventions, whether intentionally or as a side effect. For example, sumatriptan is a serotonin receptor agonist taken to help with migraines, but it also reduces serum levels of adrenocorticotropin, and will reduce cortisol levels as a result [15]. Corticosteroids, such as dexamethasone, are a synthetic form of natural cortisol and can be used as cortisol replacement or to treat inflammation. Because cortisol is one part of an interconnected system, these types of medication can have indirect effects. Increased serum cortisol levels will normally trigger negative feedback to the hypothalamus and pituitary, the first links in the HPA axis, which leads to serum cortisol levels decreasing [16]. Corticosteroids trigger the same mechanism, which means that taking them lowers cortisol levels in the long term. Thus, it is always important to consider the timeframe and downstream effects when estimating the effect of any form of medication on cortisol levels.

Once the body is familiar with the effects of cortisol-affecting medication, learning processes can modulate their effects. These generally arise through the process of classical conditioning. Classical conditioning occurs when a natural reaction, the unconditioned response, which is normally caused by a stimulus termed the unconditioned stimulus (UCS), is repeatedly paired with a different, traditionally neutral stimulus. Once an association is established, the paired stimulus, known as the conditioned stimulus (CS), may evoke a response even when the UCS is not present; in this case, the response is known as the conditioned response [17]. These principles can be applied to cortisol-affecting medication. After repeated pairings, the CS will “remind” the body of the UCS and evoke either the cortisol change produced by the medication or a compensatory feedback mechanism [18,19]. A review of human and animal studies [20] found that this type of pharmacological conditioning was effective in animals, with 13 out of 15 studies finding the expected effect but less often tested and not as effective in humans. Of the human studies performed on this topic, 2 used medication that indirectly affects cortisol levels as a UCS: Benedetti et al [21] used sumatriptan, which reduces cortisol levels, while Petrakova et al [22] used corticotropin-releasing hormone, an upstream factor in the HPA axis. In the study by Benedetti et al [21], participants were injected with sumatriptan on 2 consecutive days, and on the third day, they received a saline injection presented as a 50/50 chance of sumatriptan or saline. Cortisol levels on the third day decreased in response to the injection in this group, while no effect was observed in the group that received the same injection without the previous 2 days of conditioning. Petrakova et al [22] used 2 conditioning trials 3 days apart, where participants received a distinctly flavored and colored drink combined with an injection of corticotropin-releasing hormone. After another 3 days, the participants were tested with a saline (placebo) injection on 2 subsequent days. Compared with a control group that also received saline injections in the conditioning phase, the participants showed an increase in cortisol during conditioning, but not in response to saline.

Two other studies relied on a direct increase in cortisol. Sabbioni et al [23] used dexamethasone, a glucocorticoid, while Tekampe et al [19] used hydrocortisone. In both cases, the CS was a strongly flavored drink combined with oral intake of the UCS on 3 occasions during the conditioning period. The results here are mixed again. Both studies indicate that cortisol increased after conditioning, but the results are inconclusive because of low power or group differences at baseline, respectively. On the basis of the 4 studies investigating this topic, it remains unclear to what extent and in what situations cortisol levels are subject to classical conditioning in humans. It may be worthwhile to test cortisol conditioning in other situations.

Association learning is generally performed while the learner is fully conscious, but a line of studies suggests that it is also possible during sleep. A series of studies by the same research group [24-26] have shown that associations between a scent and another stimulus can be formed during sleep. While these stimuli are relatively subtle, they can lead to relevant behavioral effects; 1 study found that coupling the scent of smoke with an aversive stimulus for one night led to a modest reduction in smoking for several days afterward [25]. Odors seem to be particularly suited for this type of learning, because they do not wake sleeping individuals but seem to reduce arousal and wakefulness [27] and seem to function as a strong memory stimulus in general [28]. This idea is supported by other exploratory studies suggesting that presenting a scent during sleep can reactivate memories. For example, 1 study had participants perform a problem-solving task in the evening and simultaneously present a scent. On the subsequent night, some participants were reexposed to the scent, and these participants imagined and applied more creative solutions to the problem the next day compared with participants who received a different or no scent [29]. The authors suggest that this effect was the result of reactivating memory of the task during sleep. Another study [30] similarly presented a scent during sleep that was also present during a task performed the evening before, in this case using a visual memory task. In addition, while the scent was presented, functional magnetic resonance imaging measures were taken to examine brain activity. The results showed that the presentation of the scent activated the hippocampus, known for its role in declarative memory, and improved memory performance the following day, suggesting that scents presented during sleep can reactivate memories and influence objective outcomes.

Two animal studies have indicated that this type of learning may apply not only to associations relevant outside of sleep but also to the workings of the diurnal rhythm itself. In 1 study, a CS that was previously associated with light exposure was found to be able to trigger behavioral awakening patterns and awakening-related activity in the suprachiasmatic nucleus [31]. In another study, a stimulus linked to light deprivation was able to trigger increased melatonin levels related to the start of sleep [32]. To our knowledge, these results have not been replicated in humans. However, 1 publication suggests that the diurnal pattern of cortisol concentration can be influenced by learning [33]. When participants were informed that they would be awoken 3 hours before normal, they showed an anticipatory increase in adrenocorticotropin several hours before awakening. This response was not present when the participants were not given any warning, regardless of whether they were awoken 3 hours before normal or simply allowed to keep sleeping. This suggests that the human diurnal rhythm may be subject to learning effects just as it is in animals.

**Figure 1 figure1:**
[figure not shown]
Stylized representation of a typical change in cortisol levels over a 24-hour period. CAR: Cortisol Awakening Response.

### Objective

This study builds on these separate lines of evidence by investigating whether the CAR can be conditioned during sleep and moved to an earlier point in the night. Manipulation of the CAR could help evoke the benefits associated with a high CAR, such as a more alert and prepared awakening on busy days, or a low CAR, such as a more restful awakening. The association between cortisol and the diurnal cycle may indicate that such effects could be helpful in normalizing the sleep-wake cycle when it has been disturbed, as seen in conditions such as seasonal affective disorder [34] or delayed sleep phase disorder [35]. These effects are especially valuable considering that they could be evoked without the use of medication and the associated side effects.

Owing to the interindividual reliability and strength of the CAR, it has the potential to be an effective unconditioned response. By exposing participants to a distinctive odor in the half hour before awakening, we expect that an association can be created between the cortisol increase in this period and the distinctive scent. According to the principles of classical conditioning, the scent alone should also be able to evoke an increase in the CAR and potentially accompanying feelings of wakefulness, even when administered hours before the regular time of awakening.

## Methods

### Ethics Approval and Dissemination

The study was approved by the Medical Ethics Committee of the Leiden University Medical Centre, Leiden, the Netherlands (case NL62812.058.017), who will be notified of major changes. The study is performed in accordance with the principles of the Declaration of Helsinki and Dutch Medical Research Involving Human Subjects Act (WMO). The study was preregistered at the Dutch trial register [36]. The results will be disseminated in peer-reviewed journals, international conferences, and the PhD thesis of the first author.

### Participants

Participants are recruited from the local Dutch population and compensated with €100 (US $110.25) for participation. Flyers displaying a summary of the study inclusion criteria and procedures as well as the compensation amount are disseminated on social media through word of mouth by students and teachers, in university buildings, and in local student housing. Owing to the novel and exploratory nature of the study design, no sufficiently similar studies are available to form the basis of a power analysis. Studies on similar topics have used different outcome measures and statistical analyses and thus do not offer a usable comparison. Therefore, it was decided to run a pilot study and include as many participants as possible within the grant-permitted timeframe, which resulted in 50 inclusions and 42 participants completing the full protocol. It should be noted that the most similar studies available use a comparable number of participants [24,25,37].

To avoid confounding in the measurement of the CAR by menstrual cycle or age [38], only male individuals between the ages of 21 and 34 years are included, and participants are excluded if their answers during screening indicate obesity (defined as BMI >30 kg/m^2^), brain damage, or HPA axis–related endocrine disorders (Cushing disease or Addison disease). Participants currently taking medication (including glucocorticoid medication) or who have a habit of heavy drinking or recreational drug use are also excluded. Participants are screened for severe somatic or psychiatric conditions that would interfere with the study protocol using the Mini-International Neuropsychiatric Interview Plus (MINI-Plus) [39]. To ensure a regular sleep pattern, participants are screened using the Pittsburgh Sleep Quality Index (PSQI) [40] and excluded if they experience jetlag or participate in shift work up to 1 week before participation. To ensure that participants are able to properly detect the scents used in the study, they are excluded if they indicate that they have olfactory impairments. Participants are also excluded if they report allergies or sensitivity to perfume or similar substances that might indicate an adverse reaction to the scents used in the study or if they show an allergic reaction to the scents in the course of the study.

Ongoing health and stress are checked at several points from 1 week before participation up to the conclusion of the study, and participants are encouraged to report any changes between these points. Participation is stopped if a participant uses glucocorticoid medication, has high levels of stress, or falls ill during the study period. The participants are asked to refrain from alcohol and drug use for the duration of the study. Caffeine use is permitted for consistency with existing habits but is monitored. They note their regular awakening time and are requested to set their alarm at exactly the noted time and maintain a steady sleep rhythm for the duration of the study. All participants sign an informed consent before participation.

Upon inclusion, participants are randomized to the experimental or control group through a pregenerated random number list, set to randomize in blocks of 4. Owing to procedural constraints (see the *Procedure* section), the study is single-blinded. Participants are not informed about the existence of a control group or the purpose of the study until the debriefing at the end of the study; instead, they are told that the study examines the effect of certain scents on sleep.

### Design

The study design is summarized in Figure 2. Participants follow a 2-week protocol, with all measurements taking place in their own homes. The first week functions as a baseline measure. In the second week, the scent conditioning takes place on Tuesday through Thursday morning. Participants are exposed to a scent half an hour before awakening, with the aim of conditioning the scent to the CAR. The 30-minute interval was chosen to match the CAR in length and to increase the chance that the participant is still asleep for the length of the scent presentation, while still clearly preceding the CAR and minimizing the time between CS and CAR. It is presupposed that the CAR naturally functions as an unconditioned response to daylight and other zeitgebers that set the diurnal rhythm that serves as the UCS. The final night of the study functions as the test phase. To test whether conditioning has taken place, participants in the experimental group are asked to set their alarm 4 hours earlier than normal, and the scent device releases the trained scent half an hour before this time. This way, the CS is present, while the UCS is not. Participants in the control group wake up at the same time, but for them, the scent has surreptitiously been replaced the previous day with a different, novel scent, so that neither the CS nor the UCS is present. We expect that in the experimental group, the scent (CS) will evoke the CAR and lead to an increase in cortisol levels. While the process of awakening may lead to an increase in cortisol levels in both groups, the presence of the CS would cause this increase to be more pronounced in the experimental group.

**Figure 2 figure2:**
[figure not shown]
Study design of the protocol conditioning the cortisol awakening response. See Design and Procedure section for details on the content of each measurement. HRV: heart rate variability.

### Measurements

#### Scent Delivery System and Scents Used

Scents are delivered using the Air/Q-100 and Air/Q-160 devices and accompanying scent cartridges (Prolitec Inc). The scents used in the study were “Blue Wood” (Prolitec reference 9083) and “Marsala” (Prolitec reference 9141), with the latter used as the control scent during the last night for the participants in the control group and the former for all other instances. The scents were previously piloted to ensure that they were sufficiently distinctive. The devices release the scent at intervals of approximately 2 minutes every 9 minutes. The exact length of the delivery was dependent on the settings of the device, which were adjusted to the size of the participant’s bedroom based on the manufacturer’s suggestions. Custom-made containers were used to muffle the noise generated by the scent delivery devices.

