During the weekend and on the morning of the following Monday, participants only complete the web-based sleep diary and indicate their sleeping times on the actograph. On Monday, an experimenter arrives to install the scent delivery system. This device has been preprogrammed to deliver the distinctive scent 30 minutes before the participant’s regular awakening time. Participants continue to complete the diary and use the actometer in the second week, and starting Monday evening, they also wear the heart rate monitor every night. An experimenter comes by again on Thursday to reset the scent delivery system to go off 4 hours earlier than previously, that is, 4 and a half hours before regular awakening. The experimenter also checks the participant’s experience with the scent device at this time and notes if the participant had any unexpected reactions or has woken up early. Unbeknownst to the participant, if the participant is in the control group, the cartridge containing the scent is also switched for a different cartridge containing a different scent. The participant is instructed to set their alarm 4 hours earlier than normal and perform saliva measures at the new time of awakening and 15, 30, and 45 minutes later. They also use the web-based diary to complete the PANAS, Stress NRS, SVS, and CIS-fatigue directly after the first and third saliva measures. After the final saliva measure, the participants are allowed to return to sleep. They awake at a time of their choosing the following morning and only at that point remove the heart rate monitor. Their only remaining activity that day is a final diary filled in at a time of the participant’s choosing. Later that day, an experimenter picks up the saliva samples and all equipment, including the actometer that the participant can at that point remove, and debriefs the participant about the true aim of the study and their group assignment.

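### Test-night scent and group are the same variable (Blue Wood = experimental, Marsala = control), so a group difference or a null cannot be attributed to conditioning alone

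*Protocol article*

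**What the plan says.** Under Scent Delivery System and Scents Used, the protocol article names two fragrances, Blue Wood first and Marsala second, and fixes their roles: "the latter used as the control scent during the last night for the participants in the control group". On every other occasion, in both groups, Blue Wood is released. The same section says of the choice of fragrances: "The scents were previously piloted to ensure that they were sufficiently distinctive".

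The Design section describes the test night. In the experimental group the alarm is set four hours early and "the scent device releases the trained scent half an hour before this time". In the control group "the scent has surreptitiously been replaced the previous day with a different, novel scent, so that neither the CS nor the UCS is present". The Procedure section confirms how this is done: on the Thursday of week 2, for controls, "the cartridge containing the scent is also switched for a different cartridge containing a different scent". The scent device is first installed on the Monday of week 2, after the week 1 saliva samples.

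The Statistical Analysis section defines a conditioned effect as a larger rise from week 1 to the test night in the same-scent group than in the different-scent group. It applies this definition to the area under the curve with respect to increase and to the first cortisol value, each in a linear mixed model with week and group as fixed factors.

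**The concern.** The Design section attributes the expected group difference to learning: "the presence of the CS would cause this increase to be more pronounced in the experimental group". That attribution needs the groups to differ on the test night only in whether the scent had been trained. They also differ in which fragrance is in the room, and the assignment is fixed by arm. A larger cortisol rise in the experimental group could therefore be conditioning, a direct effect of Blue Wood relative to Marsala, or both. A null could be a true absence of conditioning, or conditioning offset by a fragrance difference in the opposite direction.

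This matters because the Discussion would read a positive result as evidence that the cortisol awakening response can be conditioned, and a null as a possible sign that conditioning of cortisol is not feasible in humans. Neither the identity of the scent nor its novelty is listed there as an alternative explanation.

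**Working it through.** The article contains no power or sample-size calculation, so there is no figure to reproduce. The check has four steps.

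**1. What the contrast estimates.** Write the expected change from week 1 to the test night as a sum of separate effects:

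- W: waking four hours early, common to both groups
- C: conditioning
- F and V: the test scent being familiar or novel
- B and M: direct effects of Blue Wood and Marsala

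Experimental: W + C + F + B. Control: W + V + M.

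Difference = C + (F − V) + (B − M).

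Week 1 has no scent, so subtracting baseline removes none of B or M.

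**2. Whether an analysis could separate the terms.** On the test night the Blue Wood indicator equals the experimental-group indicator for every participant. A design matrix with an intercept, group and test scent therefore has rank 2 instead of 3. A scent covariate would be collinear with group and cannot be estimated.

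**3. Possible size.** Suppose C = 0 and F = V, and let d be (B − M) divided by the SD of the change score. The documents give no value for d; 0.2 to 0.8 is an assumed range. Other inputs:

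- 42 completers and 50 inclusions (Participants)
- α = 0.05 (Statistical Analysis), taken as two-sided because the article does not state sidedness
- equal groups, assumed from the blocks of 4; the split of completers is not reported

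For a two-sample t test with n per group, the noncentrality parameter is d × √(n/2), on 2n − 2 degrees of freedom. With n = 21 it is 3.24 × d on 40 degrees of freedom. With n = 25 it is 3.54 × d on 48 degrees of freedom. The probability of p < 0.05, for either cortisol analysis taken singly, is:

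| Assumed d | N = 42 | N = 50 |
|---|---|---|
| 0.2 | 0.10 | 0.11 |
| 0.3 | 0.16 | 0.18 |
| 0.5 | 0.35 | 0.41 |
| 0.8 | 0.72 | 0.79 |

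Without a fragrance difference each entry would be 0.05. The bias, B − M, does not shrink as n grows; the chance of a misleading significant result rises with n, as the two columns show.

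**4. Effect of counterbalancing.** If half of each arm trains on each scent and controls are tested on the other one, both groups have the average direct effect (B + M)/2. The difference becomes C + (F − V): the fragrance term is gone and the novelty term stays. A simulation with 10 participants per cell (N = 40), test scent as a model factor, no conditioning and 40,000 runs gave rejection rates for group of 0.051, 0.050 and 0.050 at d = 0.2, 0.5 and 0.8.

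**The case against.** The strongest reply is that participants are randomised, so the comparison is sound as far as it goes. That stands. A reader might infer from complete confounding that the trial is uninformative, but the documents do not support this: the effect of the combined package, trained Blue Wood against novel Marsala, is estimated without confounding by participant characteristics. What is lost is attribution to one component.

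A reader might also take the Background as evidence that these two fragrances differ, since it says of odours that "they do not wake sleeping individuals but seem to reduce arousal and wakefulness". It does not show that. The statement concerns odours in general, both groups receive an odour on the test night, and a general odour effect cancels between groups. Only a difference between Blue Wood and Marsala biases the result, and the article reports none in either direction. Likewise, the article mentions piloting for distinctiveness, but as a condensed text it does not establish that nothing else was checked. Distinctiveness by itself does not show equal effects on cortisol or awakening.

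One might hope to size the problem from heart rate variability, comparing the first Blue Wood night with the scent-free night in week 1. This would not work. There is no Marsala night in that comparison, the outcome is not cortisol, and scent is mixed with week, weekday and the first night with a new device, at the regular waking time instead of four hours earlier.

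Finally, the study describes itself as exploratory and a pilot, and collection is closed. That limits the remedy for this dataset. It does not make the stated causal inference correct, and results are still to be published.

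**Conclusion.** The point holds as a limit on attribution. The allocation is stated outright and leaves no room for counterbalancing, so this is a design choice and not a detail left to a fuller document. A difference, or its absence, between groups cannot be assigned to conditioning alone. The bias equals the direct Blue Wood minus Marsala effect, whose size and sign are unknown. Over an assumed 0.2 to 0.8 SD, a study with no conditioned effect would give a significant group test with probability about 0.10 to 0.72 at 42 completers, or 0.11 to 0.79 at 50, assuming equal groups, a two-sided test and additive effects. These figures show sensitivity to an assumption; they are not evidence that the scents differ.

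Novelty against three mornings of familiarity is a second component aligned with group, and it would survive counterbalancing.

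**What to change.** **For the design and any further cohort.** Counterbalance scent roles within each arm: half train on Blue Wood and half on Marsala, the experimental group is tested on its trained scent, and controls on the other. Stratify the randomisation list accordingly and include test scent as a factor in both cortisol models. The same two cartridges suffice; the cost is a stratified list and one extra model term. Separating novelty from conditioning would need a further control, such as a group exposed to the scent without the pairing, which is a larger change.

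**For the closed dataset.** Change the inference in the Design, Statistical Analysis and Discussion sections, and carry it into the results report. Suggested wording:

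> On the test night the experimental group received the trained scent (Blue Wood) and the control group a new scent (Marsala). The group difference in change from week 1 estimates the effect of this combined contrast. Conditioning cannot be separated from the identity of the scent, or from its familiarity or novelty.

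The same caution should accompany a null result. This costs a few sentences. No added covariate can substitute for it.
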